### Assessment

This is a single center, double blind, randomized, 3-period 3-treatment, random-sequence crossover study. After the baseline TMS assessment, the same participants will be orally exposed to all substances (dipyridamole, caffeine, or placebo), in a random order, after a washout period. Participants and researchers involved will be blind to the substance’s nature. More in details, the “dipyridamole arm” will consist of a single oral dose of dipyridamole 75 mg, while the “caffeine arm” of a single oral dose of caffeine 200 mg. After an approximately one-hour interval (the absorption peak of dipyridamole and caffeine is known to occur in about 60 minutes after the oral intake), TMS tests will be repeated to evaluate potential effects of the active compounds compared to placebo. All capsules (active and placebo), prepared by the Pharmacy Department of the Oasi Research Institute-IRCCS, will be indistinguishable. Clinical evaluation and IRLS-RS will be repeated after each experimental condition. Discontinuation or modification of interventions will be allowed, if necessary (e.g., dose change in response to harms or worsening disease), and all the procedures needed to improve adherence to intervention protocols and monitoring will be taken into account. There will be no other relevant or concomitant treatment during the interventions.

Cognitive assessment, will be performed in the morning by a trained psychologist expert in clinical neuropsychology ([name]). Tests will cover a range of different cognitive domains, including attention, memory, verbal fluency, executive functions, and working memory. In addition, all subjects will complete: the vocabulary subtest of the Wechsler Adult Intelligence Scale, which assesses the patients’ understanding of words and reflects language development, expressive language skills, cultural and educational experiences, ability to use words appropriately, and retrieval of information from long-term memory; the Global Sleep Assessment Questionnaire, which distinguishes between sleep disorders (including no sleep disorder), also serving as a practical screening tool for primary care and sleep centers; the Pittsburgh Sleep Quality Index, an internationally validated rating scale used to provide a reliable, valid, and standardized measure of sleep quality; the Beck Depression Inventory II, a multiple-choice self-report inventory, which is one of the most widely used psychometric tests for measuring the severity of depression; the State-Trait Anxiety Inventory, which is a self-report rating scale that assesses separate dimensions of “state” and “trait” anxiety (examples of what this inventory measures include feelings of apprehension, tension, nervousness, and worry). Overall, this comprehensive battery will be used in order to assess the overall premorbid intelligence and the quality of life (QoL) of all participants, as well as to screen them for any relevant co-morbid psychiatric condition. Psycho-cognitive tests will not be repeated because of the very short time interval (one hour) compared to the first assessment.

Single-pulse TMS will be performed by using a High-power Magstim 200 mono-pulse magnetic stimulator (The Magstim Company, Whitland, Dyfed, UK). The stimulator will be connected to a 70 mm figure-of-eight coil, held over the M1 at the optimum scalp position to elicit motor evoked potentials (MEPs) in the contralateral First Dorsal Interosseous (FDI) muscle of the dominant hand, according to the Edinburgh Handedness Inventory [36]. Paired-pulse TMS will be run by connecting two magnetic stimulators to each other through a “BiStim” module (The Magstim Company, Whitland, Dyfed, UK). EMG activity will be recorded from silver/silver chloride surface electrodes. Motor responses will be amplified and filtered (bandwidth 3-3,000 Hz) using a 2-channel amplifier system, with an amplification factor of the screen of 100 μV per division unit for the measurement of rMT, and 1 mV per division unit during MEP recording. The temporal resolution of the screen will be 5 ms per division unit, in such a way that TMS artifact, the beginning, and the end of MEP are always visible.

Single-pulse TMS measures will include: resting motor threshold (rMT), CSP, MEP latency and amplitude, and central motor conduction time (CMCT). Resting MT is defined, according to the international recommendations [37], as the lowest stimulus intensity able to elicit MEP of an amplitude >50 μV in at least 5 of 10 trials, with the muscle at rest. This is a global measure of excitability, reflecting the membrane ion channel functioning and the Glu-mediated excitation state of cortico-spinal neurons and interneurons projecting onto these neurons within the M1, as well as the excitability of spinal motor neurons, neuromuscular junctions, and muscles [38]. CSP is determined as approximately 50% of maximum tonic voluntary contraction of the target muscle, induced by contralateral TMS delivered at 130% of rMT. During CSP recording, the subject will maintain the isometric tonic contraction by abducting the index finger against a strain gauge. The mean CSP duration, based on trial-by-trial measurements of 10 rectified traces, will be calculated. Following the above-mentioned guidelines [37], in each single trial, CSP is measured as the time elapsing from the onset of MEP until the recurrence of voluntary tonic EMG activity. CSP is primarily mediated by the activity of GABA-B intracortical inhibitory interneurons [39]. MEPs with the shortest latency (defined as the temporal interval between TMS artifact and the first negative deflection of the evoked motor response) will be considered for analysis, given that it is known to best reflect the conductivity along the fastest cortico-spinal axons. MEPs size is calculated as the biggest peak-to-peak amplitude of the motor responses [37]. CMCT reflects the integrity of the cortico-spinal conductivity, from the upper to the lower motor neurons. It is calculated by subtracting the conduction time in peripheral nerves from MEP latency obtained during moderate active muscle contraction (10-20% of maximum background force), at a stimulus intensity set at 130% of rMT [37].

Intracortical circuits will be studied by using the conventional conditioning-test paradigm by Kujirai and co-workers [40]. The procedure consists of applying two magnetic stimuli in rapid succession through two magnetic stimulators connected to each other. The conditioning stimulus (subthreshold) is applied at 80% of the subject’s rMT, and the intensity of the test stimulus (suprathreshold) is set at 130% of rMT. The interstimuls intervals (ISIs) tested will be: 2, 3, 5, 10, 15, and 20 ms; ten trials for each ISI will be recorded randomly. The responses are expressed as the ratio of MEP amplitude produced by paired stimulation to that produced by test stimulation alone. Short-latency intracortical inhibition (SICI) is obtained at short ISIs (2, 3, and 5 ms) in which the conditioning stimulus determines a motor suppression with respect to the test stimulus; it is attributed to an activation of the GABA-A neuronal transmission [41]. ICF is studied at longer ISIs (10, 15, and 20 ms), in which the conditioning stimulus determines an enhancement of the motor response with respect to the test stimulus. ICF is a more complex phenomenon, modulated by multiple neurotransmitters, although it mainly involves the excitatory Glu neurons, with a DAergic contribution 04 [42].

All TMS measurements will be conducted by a trained operator, expert in non-invasive brain stimulation techniques ([name]), while subjects are seated in a comfortable chair with continuous visual and EMG monitoring to ensure either a constant level of muscular activity during tonic contraction or complete relaxation at rest. Data will be collected on a dedicated database and stored for the off-line analysis [43]. Data entry, coding, security, and storage, including processes to promote data quality (such as double data check and range checks for data values) will be carefully considered. Data could not be fully anonymized, although they will be pseudonymized and safely stored. Similarly, any adverse effect during or after the procedure will be carefully collected, assessed, reported, and managed, if necessary.

When appropriate, patients will be actively involved in the implementation and refinement of the study protocol, e.g., by providing any input on the various parts of the experimental procedure and customizing the relevant outcomes. Although limitations exist due to data protection and technical requirements, efforts will be made to involve patients also in the development of the dissemination strategy, including writing a plain language summary and designing a leaflet for peers and patient groups/associations. Trial results will be communicated to participants, healthcare professionals, and relevant groups through scientific publications, conferences, seminars, and other data-sharing arrangements.

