## Materials and methods

### Study design

The study employs a double-blind, randomized, cross-over exploratory design. Each subject will receive dipyridamole, caffeine, or a placebo in a random sequence determined by computer-generated random numbers. The administration will occur during three different TMS sessions in the late afternoon (in accordance with the circadian distribution of RLS symptoms), with a sufficient wash-out period (at least 2 times the half-life of each substance) between sessions. To enhance the randomness of the sequence, planned restrictions will be unavailable to the contributors enrolling participants or assigning interventions. The allocation sequence will be implemented using sequentially numbered, opaque, sealed envelopes. Blinding of trial participants, outcome assessors, and data analysts will be maintained also after assignment to interventions.

This study (version v.1.0_14/07/2020) received approval from the research Ethics Committee “CE IRCCS Sicilia – Oasi Maria SS.” on October 25, 2016 (Approval ID: 2016/CE-IRCCS-OASI/1). It adheres to SPIRIT (Standard Protocol Items for Randomized Trials) recommendations in a clinical trial protocol and related documents (Fig 1), and it has been registered in a WHO approved registry, i.e., the ISRCTN registry (registration number: ISRCTN11559397). Any protocol amendments or relevant modifications (such as changes to eligibility criteria, outcomes, analyses) will be communicated to relevant parties, including investigators, the research Ethics Committee, trial participants, trial registries, journals, and regulators. The recruitment period for this study will range from March 01, 2024, to February 28, 2025. Written informed consent will be signed by all subjects prior to the inclusion in the study; additional consent provisions for participant data collection and use will be obtained, if necessary. Authorship eligibility of protocol contributors will follow the guidelines of the International Committee of Medical Journal Editors (ICMJE).

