### Outcomes

Primary outcomes: rMT (%), CSP (ms), MEP latency (ms) and amplitude (mV), CMCT (ms), SICI (ratio), and ICF (ratio). Secondary outcomes: correlation between TMS metrics (primary outcomes) and psycho-cognitive measures (Vocabulary subtest of the Wechsler Adult Intelligence Scale; Global Sleep Assessment Questionnaire; Pittsburgh Sleep Quality Index; Beck Depression Inventory II; State-Trait Anxiety Inventory).

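### The one-hour reason for taking the psycho-cognitive tests only once does not fit the schedule, and it leaves state anxiety unmeasured at the TMS sessions it may be correlated with

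*Protocol article*

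**What the plan says.** All places are in the protocol article, Materials and methods.

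- **Assessment**, on timing: "Cognitive assessment, will be performed in the morning by a trained psychologist expert in clinical neuropsychology". The self-report scales, including the State-Trait Anxiety Inventory, are then added without a time of their own. The article describes that inventory as having separate state and trait dimensions.
- **Assessment**, on repetition: "Psycho-cognitive tests will not be repeated because of the very short time interval (one hour) compared to the first assessment".
- **Study design**, on dosing: "The administration will occur during three different TMS sessions in the late afternoon", and the sessions are held "with a sufficient wash-out period (at least 2 times the half-life of each substance) between sessions".
- **Assessment**, on the interval within a session: "After an approximately one-hour interval (the absorption peak of dipyridamole and caffeine is known to occur in about 60 minutes after the oral intake"; TMS is then repeated.
- **Assessment**, on baseline: "After the baseline TMS assessment, the same participants will be orally exposed to all substances". The clock time of this baseline TMS is not given. Clinical evaluation and the RLS severity scale are repeated after each condition.
- **Outcomes**, secondary: "correlation between TMS metrics (primary outcomes) and psycho-cognitive measures". The State-Trait Anxiety Inventory is one of the five instruments listed. The text does not say whether baseline or post-dose TMS values are meant.

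**The concern.** The article gives one reason for a once-only battery, and its own timetable contradicts that reason. For most of the battery this does little harm, because vocabulary, habitual sleep quality, depression and trait anxiety are meant to describe the patient. State anxiety describes the moment at which the form is filled in. If it is recorded once, away from the TMS session, its correlation with TMS mixes the relation of interest with change in anxiety between the two occasions.

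The article itself treats time of day as important: it sets the dosed sessions in the late afternoon to match the daily pattern of RLS symptoms, and its Introduction describes motor-cortex excitability in RLS as varying over the day. It also describes caffeine as promoting arousal. At stake is the state-anxiety part of the stated secondary outcome.

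**Working it through.** **Step 1: does one hour fit the schedule?** The article states no figure that can be reproduced here, so the check sets the statements side by side.

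| Event | Timing given | Section |
|---|---|---|
| Cognitive assessment | Morning | Assessment |
| Dosed TMS sessions | Late afternoon, three sessions | Study design |
| Gap between sessions | Washout of at least two half-lives | Study design |
| Intake to repeat TMS | About one hour | Assessment |
| Reason for not repeating the tests | One hour after the first assessment | Assessment |

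Morning to late afternoon is longer than one hour. Because the three sessions are separated by washout, at most one of them could closely follow a single first assessment. One hour matches only the interval from intake to repeat TMS. The stated reason would hold only if the battery were given immediately before intake, and that is not where the article places it.

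**Step 2: which measures are affected?** The secondary outcome names five instruments. Vocabulary, the two sleep questionnaires, the depression inventory and trait anxiety can reasonably be taken once. The state part of the anxiety inventory cannot be carried over to another occasion in the same way. The performance tests of attention, memory and so on may also vary with state, but they are not named in the Outcomes list.

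**Step 3: what could the mismatch cost?** This is an illustration. The article gives neither a true correlation nor a morning-to-session correlation, so both are assumed.

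Inputs: n = 30 completers and alpha 0.05 (Statistical analysis); two-sided testing, assumed because the article does not say; true same-occasion correlation r = 0.50, assumed; morning-to-session correlation of state anxiety c = 0.9, 0.8, 0.7 or 0.5, assumed.

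If the morning score relates to session TMS only through the state at the session, then r_obs = r × c. Power by Fisher's z is approximately Φ(atanh(r_obs) × √(n − 3) − 1.96), with √27 = 5.196.

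| c | r_obs | atanh(r_obs) × 5.196 | Power |
|---|---|---|---|
| 1 (same occasion) | 0.50 | 2.854 | 81% |
| 0.9 | 0.45 | 2.519 | 71% |
| 0.8 | 0.40 | 2.201 | 60% |
| 0.7 | 0.35 | 1.899 | 48% |
| 0.5 | 0.25 | 1.327 | 26% |

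The smallest correlation that 30 patients detect with 80% power is tanh((1.960 + 0.842)/5.196), or about 0.49. There is therefore little room for attenuation.

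The multiplier is c and not its square root. The square root suits a stable level measured with error. Here the argument is that the quantity itself changes between occasions.

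**The case against.** The strongest reply is that the battery is there to screen and characterise patients, and one administration is enough for that. Correlating such scores with TMS compares patients with each other and does not test drug effects on anxiety. Which TMS time point enters a secondary correlation is a detail that an article may leave to the full protocol or analysis plan, so its absence is not in itself a fault. Much of this stands, and it limits the point in four ways.

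- **Drug state.** A reader might infer that the scores and the TMS values necessarily come from different drug conditions. The article does not support that. A baseline TMS before any substance exists, and if it is the one used, both sides are drug-free. That the battery itself is drug-free is also an inference, from its single administration in untreated patients.
- **Time of day.** Morning is explicit for the cognitive assessment and only implied for the self-report scales. The clock time of baseline TMS is not stated. A mismatch with baseline TMS is plausible but not shown.
- **Scope.** A reader might conclude that a null result anywhere in the secondary objective could not be interpreted. That goes too far, because the difficulty lies chiefly with one subscale of one of the five listed instruments.
- **Other measurement.** A reader might also infer that no effect on anxiety or arousal would be picked up. Clinical evaluation is repeated after each condition and adverse effects are collected. Neither replaces a state-anxiety scale, but something is recorded.

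The reply does not rescue the stated reason. Concern about retest effects could justify not repeating performance tests, but that is not the reason given, and it is a weak ground for withholding a short self-report form.

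**Conclusion.** The one-hour reason is contradicted by the article's own schedule and should go. This rests on the text alone and needs no assumption.

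The practical consequence is narrow. The correlation of state anxiety with TMS may be weakened because the two sides may come from different times of day and, only if post-dose TMS is used, different drug conditions. On the assumed range, a true correlation of 0.50 would appear as 0.45 to 0.25, with power between about 71% and 26% instead of about 81%. These figures show the direction and possible scale and are not estimates for this trial.

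The comparison of dipyridamole, caffeine and placebo on the TMS outcomes is unaffected, and so are the sample size and the screening, vocabulary, sleep-quality, depression and trait-anxiety scores. The point merits a change mainly because the repair is cheap and makes the state-anxiety part of a stated secondary outcome answerable.

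**What to change.** 1. In Assessment, delete the one-hour reason. If performance tests are still to be given once, state the actual reason.
2. Have patients complete the self-report state-anxiety form at the baseline TMS visit and at each of the three sessions during the post-dose wait, and relate each score to the TMS of the same session. Repeated values from one patient should not be pooled as if independent. Alternatively, drop state anxiety from the correlation.
3. In Outcomes, state that scores collected once are correlated with baseline, drug-free TMS only.

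The cost is two wording changes and a few extra minutes per session, within a wait that already exists and at sessions where the RLS severity scale is already repeated. No extra visit, staff or equipment is needed.

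### MEP amplitude, a primary outcome, is defined as the biggest response; a mean over the same trials would usually be a steadier measure for the within-patient drug-placebo comparison

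*Protocol article*

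**What the plan says.** The Outcomes section of the protocol article names seven TMS measures as primary: "Primary outcomes: rMT (%), CSP (ms), MEP latency (ms) and amplitude (mV), CMCT (ms), SICI (ratio), and ICF (ratio". MEP amplitude in mV is one of them.

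The Assessment section then says how each measure is formed:

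- MEP amplitude: "MEPs size is calculated as the biggest peak-to-peak amplitude of the motor responses".
- CSP: "The mean CSP duration, based on trial-by-trial measurements of 10 rectified traces, will be calculated".
- MEP latency: the rule selects "MEPs with the shortest latency", and a reason is given (conduction along the fastest axons).
- Paired-pulse measures: "ten trials for each ISI will be recorded randomly".

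The Statistical analysis section compares each outcome across the three treatment conditions by repeated-measures ANOVA or the Friedman test. What enters that analysis for MEP amplitude is therefore, on the plain reading, one selected response per patient and session.

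**The concern.** Single-trial MEP amplitudes vary from pulse to pulse. If the largest is taken as the patient's value, the result depends on one trial, and a single unusually large response sets it. Its expected value also rises with the number of responses it is chosen from, so two sessions with different numbers of usable trials differ in expectation even when excitability is the same. The expected value of a mean has no such dependence.

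The study compares drug with placebo within patients, with a target of 30. Avoidable within-patient noise in a primary outcome costs precision directly. The article already averages CSP over 10 traces, so a mean would not be foreign to its methods. It gives a physiological reason for choosing the shortest latency, but only a literature reference for choosing the biggest amplitude.

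**Working it through.** **No plan figure to reproduce.** The documents give no trial-to-trial SD or CV for MEP amplitude and no precision figure for it. The one power statement (80% at effect size 0.465) is not tied to this outcome and is not used here.

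**Inputs from the documents.** The amplitude is the maximum of the responses (Assessment). CSP is a mean of 10 traces, and the paired-pulse measures use ten trials per interval (Assessment). The count in "in at least 5 of 10 trials, with the muscle at rest" belongs to the resting motor threshold. No count is tied to MEP amplitude.

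**Assumed inputs.** k = 5 to 10 usable trials; independent trials; trial CV 0.4 to 0.8; positive, right-skewed amplitudes, either log-normal (log variance ln(1 + CV²): 0.148, 0.307 and 0.495 at CV 0.4, 0.6 and 0.8) or gamma (shape 1/CV²).

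**Step 1: trial-level variance.** The ratio is R = Var[log(max of k)] / Var[log(mean of k)], from 200,000 simulated sets per case. The log scale is used so that a proportional drug effect counts equally for both summaries.

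| Trials | Log-normal, CV 0.4 to 0.8 | Gamma, CV 0.4 to 0.8 |
|---|---|---|
| 5 | 1.9 to 2.1 | 1.4 to 1.7 |
| 10 | 2.8 to 3.2 | 1.8 to 2.4 |

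Over both models and 5 to 10 trials, R runs from about 1.4 to 3.2.

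**Step 2: total within-patient variance.** The crossover comparison also contains session-to-session variation, with log SD τ. The relevant ratio is (V_max + τ²) / (V_mean + τ²), where V_max and V_mean are the two trial-level log variances. For 10 log-normal trials and assumed τ of 0.1 to 0.3:

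- Low end (CV 0.4, τ = 0.3; simulated V_max = 0.0511, V_mean = 0.0159): (0.0511 + 0.09) / (0.0159 + 0.09) = 0.1411 / 0.1059 = 1.33.
- High end (CV 0.6, τ = 0.1; simulated V_max = 0.1058, V_mean = 0.0351): (0.1058 + 0.01) / (0.0351 + 0.01) = 0.1158 / 0.0451 = 2.57.

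The total ratio is therefore about 1.3 to 2.6.

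**Step 3: dependence on the number of trials.** With log-normal trials, going from 5 to 10 usable trials raises the expected maximum by 14.6%, 21.3% and 26.8% at CV 0.4, 0.6 and 0.8, with no change in excitability. Going from 8 to 10 still raises it by about 4 to 8%.

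**Step 4: a model that favours the maximum.** Take normally distributed amplitudes, 5 to 10 trials, and express each variance relative to the square of the measure's own mean. The ratio of maximum to mean is then 1.2 to 1.6 at CV 0.3, 0.9 to 1.1 at CV 0.5 and 0.7 to 0.8 at CV 0.7. At the two higher CVs the maximum loses little or nothing. That model fits poorly there, because it puts Φ(−1/0.5) = 2.3% and Φ(−1/0.7) = about 8% of amplitudes below zero, which a peak-to-peak amplitude cannot be.

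**The case against.** **The loss cannot be derived from the documents.** This stands. Pulse count, CV and distribution are all assumed, and Step 4 shows a model with almost no loss. A reader might infer that the definition doubles or triples the variance of the outcome. The documents do not support that as a fact. It describes only some assumed cases, and only the trial-level part of the variance.

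**The sentence may describe measurement within each trace.** It could mean that peak-to-peak size is read at its largest in each response. But no step then says how the responses are combined, so the same clarification is needed.

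**The missing pulse count may lie in the fuller protocol.** This also stands, and the absence of a count is not the point here. The point is the stated rule of taking the biggest response.

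**Unequal trial counts would not favour a treatment.** A reader might infer a drug-placebo bias from Step 3. The documents do not support it: the sequence is random, participants and assessors are blinded, and nothing suggests that counts differ by treatment. Differences would mainly add noise, and with equal counts the upward shift is common to all conditions.

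**Contamination by contraction is partly handled.** The Assessment section provides continuous visual and EMG monitoring for relaxation at rest, and data range checks. These reduce stray contractions but not ordinary trial-to-trial variability.

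**SICI and ICF.** These are formed as "the ratio of MEP amplitude produced by paired stimulation to that produced by test stimulation alone", and a reader might infer that they become ratios of maxima. The text never says that a maximum is used there, so no claim is made about them.

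**The cited recommendations may support the maximum.** They are not at hand, so this cannot be judged.

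**Weight.** This is one of seven primary outcomes in an exploratory pilot that looks for a panel of measures. No stated decision rests on MEP amplitude alone.

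**Conclusion.** The point holds in a limited form. On its plain reading, the protocol article defines a primary outcome as the largest single response, while CSP in the same section is averaged. A maximum rests on one trial and rises with the number of usable trials, so it is usually the noisier choice for a within-patient comparison.

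The size is conditional. With 5 to 10 positive, right-skewed trials at CV 0.4 to 0.8, the trial-level log variance is about 1.4 to 3.2 times that of the mean. At 10 log-normal trials with between-session log SD of 0.1 to 0.3, the total within-patient variance is about 1.3 to 2.6 times as large, and the number of patients needed for equal precision on this outcome would scale by the same factor. With normal trials on a relative scale the loss may be small or absent.

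This is a precision issue in one outcome. It does not make the trial uninterpretable. The change is worth making because it costs almost nothing.

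**What to change.** Define the primary MEP amplitude as the mean (or log-mean) peak-to-peak amplitude over all artefact-free trials, with the same number of trials in every session. Choose between the mean and the log-mean before any data are seen; the ratios above were computed for the arithmetic mean, compared on the log scale. Report the biggest response as a descriptive value. The shortest-latency rule, which has its own stated rationale, can stay.

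The same traces are used, so averaging needs no extra data collection. The downside is slightly less direct comparison with reports that use the maximum, and reporting both values largely meets this.
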